### Study population and recruitment

We have chosen to include children in 1st to 6th grade since some schools have few classes; thus, we need to include children from different ages to meet the required sample size. Based on our recent study, including > 3 500 preschoolers with accelerometer-measured physical activity [21], approximately 20% total non-participation is expected throughout the study period. Consequently, we aim to recruit a sample of 90 children from each participating school at baseline and follow-up, i.e., in total 180 children for each participating school. In total, the study population will include 3 600 children from 20 schools undertaking schoolyard reconstructions over four years (180 × 20 = 3 600).

### Inclusion/exclusion criteria

Schools undergoing schoolyard reconstruction have been chosen by the Stockholm education administration depending on their need for schoolyard renewal and geographical location to represent areas in Stockholm with different socioeconomic circumstances. The children included in the study are enrolled in the participating school, 6–12 years of age at the time of study start, in 1st -6th grade and participating with the consent of their guardians. All children that fulfill the criteria will be invited to participate. Classes for students with disabilities will be included in some schools, with no restrictions based on type or severity of disability.

### Intervention description

Since 2015, the Education Committee of Stockholm has been undertaking the reconstruction of schoolyards to address the need for evaluating their quality and exploring innovative approaches for schoolyard development. In the 2023 and 2024 City Council budget, a special initiative was allocated to the Education Committee, tasking them with developing a concept and strategy for greener, more sustainable schoolyards. After the decision was made on which schools would undergo reconstruction, Karolinska Institutet was invited to evaluate the process. Thus, Karolinska Institutet is not involved in the selection of schools but is solely responsible for evaluating the reconstruction process.

The schoolyard reconstruction process will use a participatory bottom-up co-creation development approach involving students, school personnel and researchers and be evidence-based, using prior knowledge on schoolyard features that are associated with children’s PA levels during school-hours [8]. Additionally, the schoolyard reconstruction intervention process will be discussed and acknowledged among all co-creators to increase the engagement, buy-in, feasibility, relevance and sustainability of the schoolyard reconstruction intervention as recommended by a previous meta-analysis on the effectiveness in co-creation of research [22].

Workshops will be held with children, school personnel (e.g., principal, vice-principal etc.), landscape architects and researchers, at each school before schoolyard reconstruction initiation. The workshops will process the design and dimension of what components the schoolyard renewal should encompass, reflecting local challenges and needs. At some of the schools the schoolyard renewal will take place in the existing schoolyard, whereas other schools will expand their outdoor area by including adjacent spaces (e.g., woodland area and parking ground). However, the most essential change will encompass implementation of new play features/equipment in the schoolyard such as climbing walls, balance-bars, trampolines, hills, and ball game facilities, that will be applied at most of the schools.

### Outcomes and measures

To assess the outcomes, various measurements have been used and can be seen in additional file 2. Questionnaires are distributed via email to guardians, who are asked to respond to questions about both themselves and their children. The questionnaire about schoolyard quality is answered by the child. In the first year of data collection, all questionnaires were available only in Swedish, but were thereafter translated to English, to extend the language options (additional file 3, 4 and the Strengths and Difficulties Questionnaire [23]). The questionnaire answered by the contact person on the school was only available in Swedish and has been translated to English in additional file 5. Questionnaires in Swedish can be shared upon request. Moreover, the characteristics of each schoolyard will be documented before and after reconstruction to enable the assessment of how specific features influence the observed outcomes.

### Change in physical activity levels (primary outcome)

Physical activity will be measured objectively by GT3X+ accelerometers and will be categorized as moderate to vigorous physical activity (MVPA) light physical activity (LPA) sedentary time (ST) and steps with the primarily focus on MVPA. The children will be asked which one is their dominant hand, and they will be instructed to wear the accelerometer on their non-dominant hand for 24 h for 7 consecutive days, except during water activities. The sampling frequency will be at 30 hz, and an epoch length of 5 s will be used as recommended for children and adolescents [24]. The software Actilife will be used to download the data from the accelerometers and the data will then be analyzed using the open-source R package GGIR [25].

To assess the impact of the schoolyard reconstruction on children’s physical activity, we will categorize their activity levels during school hours and outside of school hours. Since many children in this age group attend afterschool care, which takes place outside of regular school hours but still occurs on school premises, guardians will be asked to indicate whether their child attended afterschool care and the time they finished.

### Change in musculoskeletal fitness in children (secondary outcome)

Musculoskeletal fitness will be measured as hand grip strength using an analogue dynamometer (TKK 5825, Grip-A, Takei, Tokyo, Japan). Two measurements will be taken on each hand and will be rounded to nearest 0.5 kg.

### Change in psychosocial functioning in children (secondary outcome)

Psychosocial functioning in children will be assessed by a parental proxy report of the Strengths and Difficulties Questionnaire [23]. A total score will be generated by adding the scores from all scales, except the prosocial scale, resulting in a range between 0 and 40. Higher score means worse outcome. Further, happiness will be assessed using a single-item Face Scale [26], consisting of seven smiley faces, answered by the children.

### Change in sleep in children (secondary outcome)

Children’s sleep will be measured by the GT3X+ accelerometers. Algorithms integrated in the GGIR package will distinguish sleet timing, duration, and continuity [27].

### Change in children’s perception of the schoolyard quality (secondary outcome)

A questionnaire with 7 items, previously used to evaluate schoolyard reconstructions [28], will be used to assess children’s perception of the schoolyard quality.

### Children’s screentime (secondary outcome)

Guardians will report their child’s screen time by answering questions about the average duration of screen use (in minutes) on weekdays and weekends, respectively.

### Children’s opportunities to be physically active outside of school (process outcome)

Parents will provide information about their child’s mode of transportation to and from school, if the child participate in organized sports, as well as their own physical activity habits.

### Schoolyard reconstruction costs (secondary outcome)

Detailed budget costs for each schoolyard reconstruction, e.g., play equipment, construction and maintenance costs will be collected for each separate schoolyard reconstruction and further used for cost-effectiveness analysis (CEA) and a cost-benefit analysis (CBA). In the CEA, we will compare the costs of the intervention to the health outcomes achieved. The CBA will go further to include monetary valuation of environmental benefits.

### Environmental impact of schoolyard reconstruction (secondary outcome)

To assess the environmental effects of the schoolyard reconstructions, we will analyze changes in tree coverage and surface reflectivity (albedo, Δα) using detailed architectural drawings. Additionally, we will obtain temperature and PM2.5 (particulate matter) data from the Environment and Health Department to evaluate changes in air quality and thermal environment associated with the increased greenery.

### Incidents in the schoolyard (secondary outcome)

Number of incidents (e.g., violence, conflicts, sun burns etc.) from before to after schoolyard reconstruction will be collected from the schools.

### Demographic variables

Socioeconomic status will be measured using parental education, asked about in one of the questionnaires. Age and sex will be determined from the social security number [29], collected through the consent forms. This number includes the individual’s date of birth, and the second-to-last digit indicates the individual’s sex. If the last digits of the social security number are missing, sex will instead be determined based on questionnaire data. Parents will also be asked to report their occupation, country of birth, and the height and weight of both themselves and their children.

### Statistical analysis

Descriptive characteristics of the participants will be summarized using summary statistics.

The unit of analysis will be children nested within schools using a random effect. Generalized linear mixed models will be used to analyze changes in time spent at different physical activity intensities and secondary outcomes, comparing measurements taken before and after the schoolyard reconstruction. When appropriate, compositional data analysis will be employed to examine all daily activity—physical activity, sedentary time, and sleep—behaviors collectively [30]. This approach treats these behaviors as interdependent parts of a finite whole (i.e., the 24-hour day), acknowledging that an increase in time spent in one behavior necessarily results in a decrease in one or more of the others. Rather than focusing on isolated changes (e.g., an increase in MVPA alone), compositional data analysis allows for the analysis of shifts in the balance among all daily behaviors. The compositional outcome will be expressed through isometric log-ratio transformations, which recognize that each behavior’s duration is meaningful only in relation to the others. For easier interpretation, isometric log-ratios will be back-transformed into minutes to illustrate how the intervention influences the distribution of time across movement behaviors.

Physical activity will be further analyzed by distinguishing between time spent during school hours, at recess, and outside of school hours. As described in the Study Design and Setting section, temporal variation across calendar years will be controlled by including a period-of-measure indicator together with the intervention indicator (pre- or post-intervention measure).

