## Materials and methods

### Study design and setting

The current study will be designed as a stepped-wedge intervention where schools undertaking schoolyard reconstruction will act as both control and intervention schools [16]. A cross-sectional sample of children in 1st to 6th grade will be measured annually in all participating schools. Children will not be tracked longitudinally; therefore, the pre- and post-intervention samples will not necessarily include the same individuals. As a result, we avoid the issue of individuals being older at follow-up. Each year, five schools located in Stockholm County will receive the intervention—schoolyard reconstruction—during the summer breaks of 2024, 2025, 2026, and 2027 (see Fig. 1). The schools will act as control sites during the spring before the reconstruction and as intervention sites in the spring after the reconstruction. This design allows us to adjust for within-school characteristics, as each school serves as its own control. Additionally, by scheduling data collection at similar time points before and after the intervention within each school, we seek to minimize the influence of seasonal variation, which may affect outcomes such as children’s physical activity levels [17]. Furthermore, a stepped-wedge study design [16], is susceptible to year-to-year variation, and will therefore be confounded by time [18]. To address this, the five schools receiving their baseline measurements during the same spring period in which the intervention schools receive their follow-up measurements will be included in the analysis, allowing us to adjust for temporal variation across years. This report follows the SPIRIT reporting guidelines [19], with a checklist provided in additional file 1.

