### Time plan of the project

This project entails an evaluation of five schoolyard reconstructions per year, in total 20 schoolyard reconstructions over four years. The reconstruction process is estimated to take between three to four months during the summer break. The schoolyard reconstructions were originally scheduled for 2023–2026. However, due to a recent increase in reconstruction costs, the projects planned for 2023 was postponed to 2024. Consequently, the follow-up data collection for the first five schools will now take place the spring of 2025 as shown in Fig. 1.

The recruitment of participants began in May 2023 and follow-up measurements for the first group of schools will take place in spring 2025. The remaining schools are expected to follow to the time plan, with recruitment expected to be completed by spring 2028 (see Fig. 1). The trial has been registered on ClinicalTrials.gov the 19th of May 2023 with the reference number NCT05865782. This is the first version of the protocol. Any changes to the protocol will be communicated to the trial registry.

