The study does have some limitations. Schools are selected based on their geographical location to represent different socioeconomic groups in Stockholm and their need for schoolyard reconstruction. As a result, the schools are not randomly selected, which can introduce potential biases. By excluding schools that may not require reconstruction as urgently, the study population may differ from the broader target population, potentially affecting the generalizability of the findings. There is also a limitation in the study design; schools serve as their own controls rather than having parallel and separate control groups, which leaves the design more susceptible to seasonal variation, which must be accounted for in the statistical analysis. Additionally, certain measurements, such as the height and weight of the children and guardians, are obtained through self-reported questionnaires rather than objective methods. This may lead to inaccuracies in the data, as self-reported measures are often less reliable.

This study will provide valuable insights into the impact of schoolyard reconstruction on climate mitigation and children’s physical activity. The findings can inform new guidelines and offer evidence to guide future schoolyard renovations, promoting increased physical activity and enhanced climate mitigation in more urban schools.

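### If each school is surveyed only once before and once after, the year-adjusted effect is not an own-control comparison; the article also contradicts itself on the number of surveys

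*Protocol article*

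**What the plan says.** Study design and setting describes a control survey in the spring before reconstruction and an intervention survey in the spring after, with five schools reconstructed in each of four summers. It then claims: "This design allows us to adjust for within-school characteristics, as each school serves as its own control". To handle year-to-year change it adds the five schools whose baseline falls in the same spring as another wave's follow-up.

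Study population and recruitment sizes this as two surveys per school: "we aim to recruit a sample of 90 children from each participating school at baseline and follow-up", and "the study population will include 3 600 children from 20 schools undertaking schoolyard reconstructions over four years (180 × 20 = 3 600".

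One sentence in Study design and setting says something else: "A cross-sectional sample of children in 1st to 6th grade will be measured annually in all participating schools".

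Statistical analysis specifies children nested in schools through a random effect, and states that "temporal variation across calendar years will be controlled by including a period-of-measure indicator together with the intervention indicator".

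The Discussion lists the own-control feature as the first strength, covering socioeconomic status and school policies. Among the limitations it says that "schools serve as their own controls rather than having parallel and separate control groups".

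**The concern.** The own-control claim and the year adjustment are presented as working together. With two surveys per school they compete. A school's change from before to after is also a change from one spring to a later one. Once each spring has its own term, nothing within a school separates the two.

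What remains is a comparison between schools in different waves, which is what the design claim says is avoided. Stable differences between early-wave and late-wave schools, including socioeconomic ones, can then enter the primary estimate. Readers of the article would believe that these had been removed by design.

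**Working it through.** **Inputs.** Four waves of five schools; 90 recruited and at least 70 required per survey; SD 20 min; target 5 min; power 0.90 (Sample size; Study population and recruitment). Wave 1 baseline in spring 2023 and follow-up in spring 2025 (Time plan of the project). The later waves are taken one year apart, ending in spring 2028, so five springs are observed. Assumed here because not stated: two-sided α of 0.05, ICC 0.01 to 0.20, and a period indicator with one level per spring.

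**The plan's own figure.** n per condition = 2 × 20² × (1.960 + 1.282)² / 5² ≈ 336.2, so 337. Over five schools this is 67.4, so 68 per school, close to the stated 70. It reproduces only when a wave of five schools is pooled and clustering is ignored.

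**Number of surveys.** 20 × 2 × 90 = 3 600 matches the stated total. Annual surveys of all schools over five springs would give 20 × 5 × 90 = 9 000.

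**Identification with two surveys.** Let θ be the effect and π the spring effects. The within-school changes are:

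- Wave 1: θ + (π2025 − π2023)
- Wave 2: θ + (π2026 − π2025)
- Wave 3: θ + (π2027 − π2026)
- Wave 4: θ + (π2028 − π2027)

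That is four equations in five unknowns (θ and four year steps). In matrix form, 20 school effects and five spring indicators have rank 24, and adding the intervention column leaves it at 24. Dating the wave 1 baseline to 2024 changes nothing, because it is still alone in its spring. With annual surveys of all schools the rank rises from 24 to 25, so the effect is identified within schools.

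**What the planned model estimates.** With school random, generalised least squares on the 40 school-survey means (n = 70, SD 20, ICC 0.05) gives

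θ̂ ≈ 0.305 (W1 post − W2 pre) + 0.39 (W2 post − W3 pre) + 0.305 (W3 post − W4 pre).

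The weights are about 0.31/0.37/0.31 at ICC 0.01 and 0.30/0.40/0.30 at ICC 0.20. The wave 1 baseline and the wave 4 follow-up have weight 0: 5 × 90 + 5 × 90 = 900 of the 3 600 planned children.

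**Exposure to school differences.** Net weights on stable wave levels are +0.305, +0.086, −0.086 and −0.305 for waves 1 to 4. Hence

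bias ≈ 0.305 × (wave 1 − wave 4) + 0.086 × (wave 2 − wave 3).

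With waves 2 and 3 equal:

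| Assumed wave 1 − wave 4 gap | Bias | Share of 5 min |
|---|---|---|
| 2 min | 0.6 min | 12% |
| 4 min | 1.2 min | 24% |
| 6 min | 1.8 min | 37% |

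**First stage** (wave 1 plus the wave 2 baseline). The estimate is exactly W1 post − W2 pre at every ICC. The wave 1 baseline is unused, and the full difference between waves 1 and 2 passes through.

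**Cross-check on the SE (full data, n = 70).**

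| ICC | With spring terms | Without |
|---|---|---|
| 0.01 | 0.96 | 0.75 |
| 0.05 | 1.24 | 0.74 |
| 0.10 | 1.52 | 0.72 |
| 0.20 | 1.95 | 0.68 |

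A within-school comparison does not lose precision as the ICC grows. The year-adjusted one does, which marks it as a between-school contrast.

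**The case against.** The strongest reply is that two surveys per school is only one of two designs in the text. If all schools really are measured every spring, the effect is identified within schools and the problem disappears. The timing figure is not available to settle this. That stands: the failure is conditional. But the recruitment total fits only two surveys, and so does the use of the next five baseline schools as the concurrent comparison. One of the two statements must change either way.

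Second, a random school effect with period terms is a recognised stepped-wedge model, and it is unbiased if waves have equal expected levels. This also stands. The model runs and returns an estimate; what is missing is the within-school identification claimed for it.

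Third, the article discloses that schools were not randomly selected and that there are no parallel controls. It does not draw the consequence for the adjusted estimate, so disclosure softens the point without answering it.

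Two stronger readings are tempting and are not supported. A reader might infer that the city ordered the waves by need. Inclusion/exclusion criteria and the Discussion describe how schools were chosen, not how they were allotted to summers. All that can be said is that no randomised order is described. A reader might also infer that the own-control element vanishes altogether. That is literally so at the first stage only; in the full analysis the school levels of waves 2 and 3 largely cancel.

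**Conclusion.** The point holds in conditional form. The article contradicts itself on the number of surveys per school. If two stand, the year-adjusted estimate depends on waves being comparable, and the own-control property claimed in Study design and setting and in the Discussion does not apply to it. Exposure is about 0.3 of the difference between wave 1 and wave 4 schools in the full analysis, and all of the difference between waves 1 and 2 at the first stage.

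The identification result needs no ICC; it rests on two surveys per school and one indicator per spring. The weights rest on assumed ICCs but barely move between 0.01 and 0.20. The gaps of 2 to 6 minutes are illustrations: nothing in the article shows that such a gap exists, so bias is a possibility and not a demonstrated fact.

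**What to change.** 1. Reconcile Study design and setting with Study population and recruitment on how many surveys each school has, and make the total agree.
2. If two surveys stand, correct Study design and setting and the Discussion (strengths and limitations). They should say that the year-adjusted estimate relies on schools being comparable across waves, and that it is not an own-control comparison.
3. Report the within-school pre-post estimate without period terms beside the year-adjusted one, stating that it assumes no calendar-year change.
4. Adjust the year-adjusted model for parental education, including its school mean. Demographic variables shows that it is already collected.

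The cost is a little more analysis and a weaker design claim; no new data are needed.

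An option, not a requirement, is to spread the same total over annual surveys of all schools: 36 × 20 × 5 = 3 600. With 80% analysable and ICC 0.05, the SE would be about 1.28 (random school effects) or 1.33 (fixed), against 1.23 for two surveys with 72 analysable each, and the effect would be identified within schools. That figure assumes all five springs are used, which is no longer possible for springs already past. The option also adds school visits and falls below the minimum of 70 per school per measurement in Sample size.
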